## Abstract

**Background:**

Health education is one of the main items to enable health promotion to patients with fibromyalgia. The objective of the study “Amigos de Fibro (Fibro Friends)” is to evaluate the impact of an educational intervention associated with physical exercise based on the web in promoting health and quality of life of patients with fibromyalgia in Brazil.

**Methods:**

A study with a randomized controlled trial approach will be carried out. The sample will consist of 24 participants, divided into two groups, with 12 individuals each. The experimental group will participate in meetings with lectures, debates, conversation rounds and exercises by a multidisciplinary team. Physical exercises will also be performed in an online environment. On the other hand, the control group will receive an e-book of education and self-care. Primary outcomes will be quality of life. The secondary outcomes will be sociodemographic and health profile, pain intensity, sleep quality, self-care agency, usage and costs of health and social care services, viability of the program and program participation. In addition, a qualitative evaluation process will be carried out with the participants. After the intervention, the data of both groups will be collected again, as well as after 3, 6, and 12 months to verify the effect and the maintenance of the intervention.

**Discussion:**

The results will provide data for studies to consider the use of this tool in the future by professionals working in the field of rheumatology.

**Trial registration:**

The protocol was registered in the Brazilian Registry of Clinical Trials RBR-3rh759 (https://trialsearch.who.int/Trial2.aspx?TrialID=RBR-3rh759). Date of registration: 07/02/2020].

## Administrative information

Note: the numbers in curly brackets in this protocol refer to SPIRIT checklist item numbers. The order of the items has been modified to group similar items (see http://www.equator-network.org/reporting-guidelines/spirit-2013-statement-defining-standard-protocol-items-for-clinical-trials/)

## Introduction

### Background and rationale {6a}

Fibromyalgia is one of the most common causes of generalized chronic musculoskeletal pain in the adult population. There is no consensus on the etiology or pathophysiology of fibromyalgia; many theories have been developed. However, it is generally accepted that fibromyalgia is a multifactorial health condition. That is, the symptoms of the syndrome develop and are maintained based on the interaction of several factors at the biological, psychological, and social levels [1]. The worldwide prevalence of fibromyalgia in the population is 0.2 to 6.6%. In Brazil, this prevalence is 2.5% [2], being higher in women, representing between 2.4 and 6.8%. In addition, in urban areas, prevalence reaches 0.7 and 11.4%, and in rural areas between 0.1 and 5.2% [3]. Studies also point to the presence of fibromyalgia in men [4–6]. Although the prevalence of fibromyalgia does not have the same notoriety as other rheumatologic conditions, its annual economic impact is considered very high [7, 8]. People diagnosed with fibromyalgia also make greater use of health services, especially in medical consultations in primary care and specialized care in several countries [1, 9].

The European Alliance of Associations for Rheumatology (EULAR) recommends the use of non-pharmacological therapies as a first-line intervention for patients with fibromyalgia, with patient education and physical exercise being an indispensable combination in the management of symptoms [10]. Physical exercise is one of the most accepted modalities. Studies have shown that physical exercise was well tolerated by patients with fibromyalgia. These studies achieved positive effects on pain intensity, fibromyalgia impact, hyperalgesia, physical function, catastrophizing, and psychological distress, without major adverse events [11–15]. Health education is one of the main items to enable the health promotion of patients with fibromyalgia. This strategy should prepare people to take control and responsibility for their own health and the health of their environment, as well as prepare them for empowerment, decision-making, participation, social control and action on the conditions, and determinants of their health and quality of life. Due to the chronic nature of fibromyalgia, patients deal negatively with this syndrome and its consequences and, to address this problem, educational programs that promote the self-management of the syndrome have been recommended to promote the health of people with fibromyalgia [16–18].

Self-management programs through educational practices are designed to help patients master the tasks needed to live with a chronic condition. Based on concepts of self-efficacy, they aim to increase a person’s confidence and ability to exercise control over worrisome health symptoms. Self-management programs have been identified as an effective means to improve quality of life and health functions, reducing the use of health resources [19–21]. Pain self-management interventions are recommended as an essential component of evidence-based clinical practice guidelines for persistent pain [21, 22].

Web-based group self-management interventions demonstrate better outcomes in small and specific populations of patients suffering from pain [20, 21, 23]. In addition, few studies to date have explored the role that web-based self-management programs can play in reducing fibromyalgia symptoms and increasing alternative methods of pain control [24]. High-quality studies are necessary to determine the effects of web-based interventions focusing on the therapeutic education of patients with fibromyalgia to promote health in primary health care in Brazil. Arnold and Clauw [25] highlighted the need to develop new biopsychosocial approaches for the treatment of fibromyalgia that focus on the management of symptoms in addition to pain through practices involving patient education. In addition, these authors highlight the lack of studies that measure significant clinical changes, which would allow a better clinical interpretation of the results of the investigation [1].

### Objectives {7}

The primary objective of the “Amigos de Fibro (Fibro Friends)” study is:

To evaluate the effectiveness of a web-based educational intervention associated with physical exercise to promote the health and quality of life of people with fibromyalgia in Brazil.

The secondary objectives are four:To verify the effect of an educational intervention associated with physical exercise via the web on pain intensity, sleep quality, and self-care management in patients with fibromyalgia.Measure the use and costs of social and health care services and the feasibility of a web-based educational intervention associated with physical exercise aimed at patients with fibromyalgia.To identify the adherence of individuals with fibromyalgia participating in an educational program associated with physical exercise to promote health via the web.Evaluate the maintenance of results obtained in individuals participating in an educational program associated with physical exercise for health promotion via the web in the short, medium, and long term.

### Trial design {8}

A study with a randomized controlled trial approach will be carried out. For the design of this study approach, a recommendation guide was considered, based on methodological points that must be followed in the textual description of the studies, the Consolidated Standards of Reporting Trials Statement (CONSORT). Objectivity and subjectivity cannot be thought of as opposites, as a quantitative study can raise questions to be deepened qualitatively, and vice versa. In this sense, a qualitative study will be carried out. Qualitative studies aim to relate the question of intentionality and meaning as inseparable from human actions, structures, and social relations. For the design of the qualitative study, the Consolidated Criteria for Reporting Qualitative Research (COREQ) was considered which is a checklist with evaluation criteria for qualitative research reports using interviews. This study is the first in Brazil and seeks to be a reference in the country so that in the future, it will be a model to be applied in all Basic Public Health Units in Brazil. Initial studies with these characteristics are recommended for studies focused on public health, in order to implement evidence-based interventions [26–30]. The flow of participants is shown in Fig. 1.

**Fig. 1 Fig1:**
[figure not shown]
Flowchart of the study recruitment procedure

## Methods: participants, interventions and outcomes

### Study setting {9}

The study will be carried out through the Google Meet® online platform (a free and easily accessible videoconferencing platform developed by Google that allows users to host and participate in virtual meetings, video calls and webinars, offering features such as screen sharing and the ability to schedule and record meetings). The participant will be able to access it through smartphone, tablet, or computer in a synchronous way.

The study will be carried out in Brazil, allowing the participation of people from all states. In addition, the study is being carried out by researchers from the “Program in Rehabilitation Sciences, Department of Physiotherapy, Speech-Language Pathology and Audiology, and Occupational Therapy, Faculty of Medicine, University of São Paulo, Brazil”.

If necessary, participants may receive training or instructions for using the Google Meet® platform. This will be questioned before starting the study, on which the tool domain by the participant. Participants will be instructed to verify that the devices they will be using have access to the Google Meet® online platform and an internet connection.

Before starting the intervention, there will be a time agreed upon by the participants for the weekly meeting. In addition, participants will receive a weekly link to access the videoconference.

Furthermore, all participants will receive instructions to follow a Code of Conduct based on the Scientific Electronic Library Online (SCIELO). This code, guided by the principles and practices of Diversity, Equity, Inclusion and Accessibility, aims to create an open, healthy, and safe environment for all participants of an online event. All people involved in “Amigos de Fibro (Fibro Friends)” will be expected to be respectful and inclusive during their participation, avoiding threats of violence, the use of harmful, harmful or prejudiced language (including prejudice related to disabilities, race, nationality, sexual orientation, gender, age, among others), personal attacks, or any form of harassment. This type of behavior will not be tolerated, and participants who do not follow the code of conduct will be subject to being removed from the ongoing project and prevented from participating in future projects organized by those responsible for the research. If any participant has questions, witnesses violations of the code of conduct, or feels attacked, that is, a victim of harassment or any type of harassment, they will be instructed to contact the responsible researchers.

Finally, each meeting will be structured in at least three basic moments:Initial moment of preparation of the group for the day’s work (engagement dynamics, warm-up, relaxation);Intermediate moment in which the group got involved in varied activities, which facilitated their reflection and elaboration of the theme developed;Moment of systematization and evaluation of the day’s work, which allowed participants to visualize their production as a work group.

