### Intervention description {11a}

#### Study groups

##### Intervention

The meetings will be organized by two physiotherapists, who will invite a multidisciplinary team working in primary care to give lectures and hold debates, rounds of conversation and exercises through the Google Meet platform. In addition, a physiotherapist will apply the physical exercises described in “Amigos de Fibro (Fibro Friends)”. The invited professionals will be as follows: a physiotherapist, a physician, a psychologist, a nutritionist, a nurse, a pharmacist, a speech therapist, an occupational therapist, a social worker, and a naturologist.

The activities will be conducted through an online group. In health promotion, group work makes it possible to break the vertical relationship that traditionally exists between the health professional and the subject of their action, which is a strategy that facilitates the expression of needs, expectations, anxieties, and life circumstances, which have some impact on the health of individuals and groups. Moreover, when developing the work with groups, the professional has the chance to stimulate participants to find collective strategies to confront the problems the community faces [32]. When starting a group, the uncertainties of the participants must be considered and, therefore, it is necessary to create a safe and reliable environment [33]. It is necessary to consider that, at this moment, introductions are formal and moments of silence are common [34]. It will be necessary to observe the group’s expectations and non-verbal communication, stimulate group cohesion and keep the group’s objectives clear, relating them to the members’ needs. At this time, it is also important to establish and maintain schedules, meeting locations and a limit of participants [34]. Participants will also be informed to avoid opening new tabs or web pages, other applications, and/or other distractions at the time of the meeting.

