#### Control group

Participants in the CG will receive an educational self-care e-book that was prepared by the authors themselves and that will address the same information that was defined in the construction of “Amigos de Fibro (Fibro Friends)”. The order of the themes of the e-book will be the same as presented in the experimental group. The e-book will have weekly chapters, meaning each week you should read a chapter with the information and note the start and end date of the reading. The choice of weekly chapters is for the CG to finish participating in the study at the same time as the experimental group. Moreover, once a week, the responsible physiotherapist will call each participant of this group to ask how the reading is going and to remind them to carry it through weekly.

The final version of the e-book is comprised of 90 pages, with the title “Amigos de Fibro (Fibro Friends)”: Promoting Health in Fibromyalgia”. The e-book was created using the Canva software, a graphic design platform that allows users to create different types of visual content. In addition, it features graphic illustrations taken from Envato Elements, a subscription platform for graphic design items. The material was divided into 10 blocks with the following themes: getting to know fibromyalgia (chapter 1), health promotion and care (chapter 2), family and work (chapter 3), body practices and physical activities (chapter 4), healthy and adequate nutrition (chapter 5), health and well-being (chapter 6), pharmacological approach (chapter 7), integrative and complementary practices (chapter 8), occupational performance (chapter 9), and sleep quality (chapter 10).

The educational content refers to self-care measures that promote the health and quality of life of individuals with fibromyalgia. In order to enrich the content, improve readability and general reader captivation of the e-book, and offer the target audience the opportunity to delve deeper into the topic, references, and links were added to the end of the material, which give access to the entirety of articles, books, theses, and websites that also support the material’s theoretical framework. The e-book has already been validated and published and showed a good level of agreement among evaluators [31]. The final version of the e-book is available at http://www.amigosdefibro.com.br.

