### Criteria for discontinuing or modifying allocated interventions {11b}

There will be no special criteria for discontinuing or modifying allocated interventions.

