### Provisions for post-trial care {30}

At the end of the project (end of the 12 months of follow-up), all participants will be invited to participate in the groups in which they were not selected, in order to thank all participants in the research.

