##### Program adhesion

At the end of the program, the participants’ adherence to “Amigos de Fibro (Fibro Friends)” will be verified, using the following parameters: abandonment rate (%) and attendance rate (%). These parameters also allow us to evaluate the viability of the program [73].

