## Data collection and management

### Plans for assessment and collection of outcomes {18a}

Data will be collected by only one trained person (pre, post, and follow-up) for standardization and to avoid data duplication. The person trained to collect the data is a researcher, with training in physiotherapy and a master’s degree in the area of health promotion. In addition, the person responsible for cleaving the data is not part of the authorship and group of researchers of the study. The instruments used in the study are detailed in the methodology section. All instruments are reliable and validated. If the reader needs a detailed version of the questionnaires, with all the tests, he can request the corresponding author by email and he will receive the file (in addition to the data that are explained in the protocol).

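### The conduct rule lets a randomised participant be removed from the whole project, although {11b} says no discontinuation criteria exist, and as worded it could end outcome assessment

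*Protocol article*

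**What the plan says.** Study setting {9} sets a code of conduct for all participants and attaches a sanction: "participants who do not follow the code of conduct will be subject to being removed from the ongoing project". The same sentence adds that they may be "prevented from participating in future projects organized by those responsible for the research".

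The section on discontinuation, {11b}, consists of one statement: "There will be no special criteria for discontinuing or modifying allocated interventions".

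Three other places bear on how far removal reaches:

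- Provisions for post-trial care {30} dates the end of the project: "At the end of the project (end of the 12 months of follow-up").
- Section {18b} plans to collect the primary and secondary variables in both groups after the intervention and at 3, 6 and 12 months. It makes no exception for removed participants and does not mention them.
- Section {20c} defines intention-to-treat as analysis by assigned group, and Sample size {14} invokes it for loss of participants.

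**The concern.** There are two linked problems.

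First, {11b} is where a reader looks for rules that end a participant's allocated intervention. It says there are none, yet {9} contains one.

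Second, the sanction is removal from the project, not from the meetings. If site staff apply it as written, a randomised participant could leave follow-up because of the protocol's own rule, without having withdrawn consent. That would be a loss of outcome data after randomisation, and it would be tied to behaviour during the intervention.

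Such losses would probably not be balanced between the arms. The code binds everyone, but only the experimental arm meets live: "The activities will be conducted through an online group". In the control arm, "once a week, the responsible physiotherapist will call each participant of this group". Opportunities to breach a code for online events are therefore mostly in one arm of 12. This is an inference from the design; the article does not state it.

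**Working it through.** There is no figure in the plan to reproduce. The check compares the texts and then bounds the loss.

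**Do {9} and {11b} conflict?** Suppose removal means the sessions only: the allocated intervention ends for that person. Suppose it means the whole study: the intervention ends and follow-up may end too. Either way a conduct breach is a ground for discontinuing the allocated intervention, which {11b} says does not exist. This part does not depend on what the word project means.

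**How far does removal reach?**

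- For the whole study: the sentence in {9} contrasts the ongoing project with "prevented from participating in future projects organized by those responsible for the research", which are most naturally further studies. Section {30} places the end of the project at the end of the 12 months of follow-up.
- For the programme only: the surrounding text in {9} is about online meetings, and the Discussion uses the word project more loosely, for the Amigos de Fibro undertaking at large. Section {18b} plans collection from both groups without exception.

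The whole-study reading is the more natural one but is not certain. No section says that assessment stops after removal, and none says that it continues.

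**Does intention-to-treat close the gap?** No. As defined in {20c}, it decides the arm in which a participant is analysed. It does not say that outcomes are still collected after removal.

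**Size of the loss for one participant removed during the intervention**

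Inputs: 12 participants per arm and 24 in total (Sample size {14}); post-baseline assessments at post-intervention, 3, 6 and 12 months, which is 4 per participant ({18b}).

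- Planned post-baseline assessments per arm: 12 × 4 = 48
- Planned post-baseline assessments in the trial: 24 × 4 = 96

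| Reading | Assessments lost | Share of arm | Share of trial |
|---|---|---|---|
| Removed from the whole study | up to 4 | 4/48 = 8.3% | 4/96 = 4.2% |
| Removed from the sessions only | 0 | 0/48 = 0% | 0/96 = 0% |

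The upper figures equal 1/12 and 1/24, as they must when one person loses every post-baseline assessment. Two such removals in one arm would be 2/12 = 16.7% of that arm. The number of removals is an assumption, since the article gives none.

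**The case against.** The strongest reply is that {9} is a general behaviour rule and {11b} answers a different question. On this view a ban on threats and harassment is not a special criterion for stopping an allocated intervention, and the most that is missing is a cross-reference. The English of the article is loose, and one noun should not be made to carry a data-collection rule. The text on retention and intention-to-treat points towards continued collection, and what happens after a removal is detail that the full protocol may hold. Ending all contact could also be a deliberate safety choice where the conduct is directed at staff.

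Part of this stands. The article never says that assessment stops, removals would be rare, and the imbalance between arms is inferred. Safety can justify ending contact in a particular case, and the fix should allow for it.

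The rest does not remove the point. The conduct rule is a stated, participant-level ground for ending the intervention, and {11b} does not acknowledge it. Nor is this a complaint about absent detail: the article states a rule, states it more broadly than its purpose needs, and contradicts it elsewhere. The code is meant to keep an online event safe, which exclusion from the sessions ordinarily achieves. Data management {19} has participants assessed individually, with data entered on online forms, so assessment need not end when attendance does.

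**Conclusion.** The concern holds, as a minor point. The inconsistency between {9} and {11b} is in the current text under either reading. That the rule permits assessment to stop follows from its literal wording, which is the more natural reading but not the only one.

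The cost per removal during the intervention runs from 0 to 4 post-baseline assessments, with a maximum of 8.3% of an arm and 4.2% of the trial. This rests on 12 per arm, four post-baseline time points and a removal before the post-intervention assessment. How many removals to expect, and in which arm, cannot be determined from the article. No particular estimate or test is shown to change. The case for acting is that an avoidable loss, probably one-sided, can be prevented very cheaply.

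**What to change.** Amend {9} and {11b} so that they agree:

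- A breach of the code of conduct may end attendance at the group sessions (or, for controls, the weekly calls). List this under {11b} as a ground for discontinuing the allocated intervention.
- The participant is still offered the post-intervention, 3-, 6- and 12-month assessments, unless they withdraw consent or contact is judged unsafe.
- The participant is analysed in the arm to which they were randomised.
- The removal is counted, with its reason, in the abandonment rate that Program adhesion already plans to report ("abandonment rate (%) and attendance rate").

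The cost is one or two sentences of protocol text. The drawback is continued contact between a removed participant and the evaluator, because "Data will be collected by only one trained person (pre, post, and follow-up"). Where that contact is a worry, assessment can be limited to self-completed online forms, at the price of a different mode of assessment for that person.
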